#### 5.5.2. Secondary Outcomes

Secondary outcomes include a broad range of bleeding-related outcomes, thrombotic complications, and postoperative complications, and healthcare resource utilization. Bleeding-related outcomes include preoperative blood transfusion, the number of PRBCs administered (1, 2, 3, or ≥4 units), lowest postoperative Hb and Ht levels within 24 h postoperatively, Hb decrease (ΔHb) (defined as the difference between preoperative Hb (measured at the ED) and the lowest postoperative Hb within 24 h), the bleeding index (defined as ΔHb plus the number of PRBC transfused between the ΔHb period), the number of patients experiencing a Hb decrease of more than 2 mmol/L. Estimated intraoperative blood loss will not be recorded, as it is considered too subjective, prone to outcome reporting bias, and highly susceptible to inter-rater variability. Clinical complications such as reoperation due to postoperative bleeding or infection, sciatic neuropraxia due to postoperative bleeding or infection, postoperative hematoma, and postoperative anemia will also be recorded. Lastly, administration of tranexamic acid, fibrinogen, or platelet concentrates will also be assessed.

Thrombotic complications recorded in this study comprise myocardial infarction (confirmed by electrocardiogram), stroke (confirmed by CT), pulmonary embolism (confirmed by CT-Angiography), deep vein thrombosis (confirmed by ultrasound), and peripheral arterial thrombosis (confirmed by CT-Angiography).

Other postoperative complications as determined by the Dutch Hip Fracture Audit guidelines will be assessed and include pressure ulcers, delirium, deep or superficial surgical wound infections, wound fluid leakage, days of wound fluid leakage, congestive heart failure, and in-hospital falls (all diagnosed by the attending physician or geriatrician) [54]. Additional complications include pneumonia (confirmed by chest radiograph or positive sputum culture), urinary tract infections (confirmed by a positive urine culture), renal insufficiency (defined as a >24 mL/min/1.73 m^2^ decrease in eGFR compared to admission), in-hospital mortality (recorded in hospital records), and 30-day mortality (determined through municipality records) [54].

Additional secondary outcomes include: hospital length of stay (in days, defined as the time between ED presentation and discharge from hospital or in-hospital death), time to surgery (in hours, from ED presentation to start of surgery), hours between last DOAC intake and start of surgery (in hours, defined as the interval between the last reported DOAC intake and the start of surgery), time until DOAC therapy is restarted after surgery (in hours, defined as the time between end of surgery and first postoperative DOAC dose), total time without DOAC therapy (in hours, defined as the time between last DOAC intake and the first postoperative DOAC dose), surgical duration (in minutes, recorded from incision to closure), and discharge destination (categorized as: home, home with assistance for ADL, temporary skilled nursing care, geriatric rehabilitation care, or a long term geriatric care facility).

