## 3. Clinical Relevance

The findings of this study will be particularly significant for the hip fracture population for several reasons. There is currently no consensus on the optimal timing of surgery for hip fracture patients on DOACs, leading to considerable clinical practice variation in discontinuation protocols across The Netherlands [12,13,27,30,31]. Clear, evidence-based recommendations are urgently needed to standardize care and improve outcomes in this vulnerable and growing patient population [31,38].

If early surgery is shown to be non-inferior with respect to bleeding and thrombotic complications, this would support a paradigm shift toward performing hip fracture surgery within 24 h of last DOAC intake. This could lead to reduced hospital length of stay, faster mobilization and rehabilitation, and lower the risk of complications related to immobilization such as pressure ulcers and nosocomial infections [39,40]. Moreover, the reduction in HLOS could lead to significant cost savings for healthcare systems, as well as improved capacity and resource utilization [40,41].

If early surgery is proven inferior to delayed surgery, this study will help to define the optimal timing of surgery after DOAC discontinuation, possibly based on renal function and drug clearance. This could enable widespread (inter)national implementation of standardized perioperative protocols, ultimately contributing to evidence based, safe, and more efficient hip fracture care.

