### 4.2. Secondary Objectives

-To investigate the effect on other bleeding-related outcomes in this population (i.e., preoperative blood transfusions, pre- and postoperative hemoglobin difference, the bleeding index, amount of packed red blood cells administered, reoperation due to postoperative bleeding or infection, sciatic neuropraxia due to postoperative bleeding or infection, postoperative anemia and postoperative hematoma).-To investigate the effect on thromboembolic outcomes in this population (such as acute myocardial infarction, stroke, pulmonary embolism, peripheral arterial thrombosis, and deep venous thrombosis).-To investigate the effect on postoperative complications in this population (i.e., wound fluid leakage, pressure ulcer, congestive heart failure, delirium, renal insufficiency, pneumonia, urinary tract infections, deep or superficial surgical wound infection, and in-hospital falls).-To investigate the effect on in-hospital and 30-day mortality in this population.-To investigate the effect on hospital length of stay and discharge destination in this population.

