### 5.7. Sample Size and Rationale for Non-Inferiority

The research question of this study is framed as a non-inferiority comparison, and the sample size has therefore been calculated to test non-inferiority. This study used the most recent institutional data, as these best reflect the clinical context and patient population of this study. These institutional data showed a transfusion rate of approximately 15% in the delayed surgery group and 10% in the early surgery group, which is considered appropriate for powering a non-inferiority analysis in this natural experiment. In consultation with clinical experts, a non-inferiority margin (ΔNI) of 5% is deemed clinically acceptable to conclude that early surgery does not result in a clinically relevant increase in transfusion requirement. Non-inferiority will be demonstrated if the upper bound of the one-sided 95% confidence interval for the absolute risk difference between groups remains below 5%. Based on these assumptions, an expected event rate of 15% in the control group and 10% in the intervention group, with a one-sided alpha of 0.05 (Zα = 1.645) and a power of 90% (Zβ = 1.282), the required total sample size is 374 patients, with 187 per group.

As the sample size is based on the per-protocol population, patient inclusion will continue until 187 patients per treatment group have been included who adhered to the protocol of their respective school of treatment (Figure 2). Inclusion in a given school will stop once the required number of per-protocol patients (*n* = 187) is reached in that group. The other school will continue including patients until it also reaches the target of 187 per-protocol patients. As a result, the intention-to-treat population is expected to exceed 374 patients. Since the primary outcome is assessed during hospitalization, no loss to follow-up is anticipated. This approach provides sufficient power to robustly assess non-inferiority within the specified parameters.

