#### 5.8.2. Secondary Outcomes

Secondary outcomes will be analyzed according to the type and distribution of each variable. Continuous variables (i.e., Hb decrease, bleeding index, surgery duration, time to DOAC restart, hospital length of stay) will first be assessed for normality using graphical methods (e.g., histograms). Normally distributed outcomes will be analyzed using parametric tests, specifically independent-sample t-tests. If the distribution is non-normal, non-parametric methods, such as the Mann–Whitney U test, will be applied. Ordinal or categorical variables with more than two categories, such as the number of packed red cell units transfused, will be analyzed using the Chi-square test. Binary outcomes, including thromboembolic events, postoperative complications, and a Hb decrease of more than 2 mmol/L, will be analyzed using Chi-square tests, or Fisher’s exact test in cases where expected cell counts are less than five.

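### Two secondary outcomes classed as bleeding-related, reoperation and sciatic neuropraxia, also count cases caused only by infection, so they do not isolate bleeding

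*Protocol article*

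**What the plan says.** Section 4.2 of the protocol article sets a secondary objective: "To investigate the effect on other bleeding-related outcomes in this population". The bracketed list that spells out this objective ends with "reoperation due to postoperative bleeding or infection, sciatic neuropraxia due to postoperative bleeding or infection, postoperative anemia and postoperative hematoma".

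Section 5.5.2 repeats the combined wording, "Clinical complications such as reoperation due to postoperative bleeding or infection, sciatic neuropraxia due to postoperative bleeding or infection", in its opening paragraph. That paragraph deals with bleeding and comes before the separate paragraphs on thrombotic and other postoperative complications.

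Infection of the surgical site is also an outcome in its own right, among the other complications in Section 5.5.2: "deep or superficial surgical wound infections, wound fluid leakage, days of wound fluid leakage".

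The analysis in Section 5.8.2 is generic: "Binary outcomes, including thromboembolic events, postoperative complications, and a Hb decrease of more than 2 mmol/L, will be analyzed using Chi-square tests", with Fisher's exact test where expected counts fall below five. Neither the outcome definitions nor the analysis section separates reoperation or neuropraxia by cause.

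**The concern.** An outcome that serves a bleeding objective should count bleeding. Take two patients: one is reoperated for a hematoma, the other for a deep wound infection with no bleeding. Under the stated definition both have the same bleeding-related event.

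Reoperation for bleeding is a useful check on a transfusion endpoint. It does not depend on the transfusion decision, and it is not confined to the first 24 h as the lowest Hb, the Hb decrease and, through it, the bleeding index are. Mixing in infection cases weakens that check. At stake is the interpretation of two secondary outcomes, not the main result.

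**Working it through.** **1. The plan's own figure.** The article gives no rate for reoperation or neuropraxia. Its only sample-size figure is for transfusion, with "an expected event rate of 15% in the control group and 10% in the intervention group". In Section 5.7 the test is one-sided at 0.05 (normal quantile 1.645), the power is 90% (quantile 1.282) and the margin is 5 points. The distance to the margin is 0.05 − (0.10 − 0.15) = 0.10.

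n per group = (0.15 × 0.85 + 0.10 × 0.90) × (1.645 + 1.282)² / 0.10² = 0.2175 × 8.567 / 0.01 = 186.3, rounded up to 187, or 374 in total. The figure reproduces, and neither secondary item enters it.

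**2. What pooling does.** Let b be the bleeding-caused rate and i the infection-caused rate, with no patient having both causes. Then:

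- pooled rate = b + i in each group
- pooled risk ratio = (b_early + i_early) / (b_delayed + i_delayed), which always lies between the bleeding ratio and the infection ratio
- pooled risk difference = bleeding difference + infection difference

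**3. Illustration.** All rates are assumed. Bleeding is held at 2% early v 1% delayed (risk ratio 2.0).

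| Infection, early v delayed | Pooled, early v delayed | Pooled risk ratio |
|---|---|---|
| 2% v 2% (no difference) | 4% v 3% | 1.33 |
| 1% v 2% (lower with early surgery) | 3% v 3% | 1.00 |
| 2% v 1% (higher with early surgery) | 4% v 2% | 2.00 |
| 3% v 1% (higher still) | 5% v 2% | 2.50 |

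Dilution in the first row needs no effect on infection. There the risk difference stays at 1 point, but its standard error at 187 per group rises from √[(0.02 × 0.98 + 0.01 × 0.99)/187] = 1.26 points to √[(0.04 × 0.96 + 0.03 × 0.97)/187] = 1.90 points. The other rows show that the direction of any further shift depends wholly on how infection behaves.

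**4. Power at 187 per group.** Exact calculation with Fisher's test, two-sided 0.05, counting significance in the direction of harm:

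- bleeding alone, 2% v 1% (about 3.7 v 1.9 events): about 4%
- pooled, 4% v 3%: about 4%
- pooled, 4% v 2%: about 12%
- bleeding alone, 3% v 1% (about 5.6 v 1.9 events): about 15%
- pooled, 5% v 3% (the same bleeding with infection 2% v 2%): about 10%

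Both bleeding-alone cases have average expected counts below five (2.8 and 3.7 per group), so the plan's own rule selects Fisher's test. The pooled cases exceed five and would take the chi-square test, which is less conservative. A normal approximation gives about 28% for 3% v 1% and about 17% for 5% v 3%. On either calculation power is low, split or pooled.

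**The case against.** The strongest reply is that this changes little. Non-inferiority is defined for transfusion only (Sections 4.1, 5.7 and 5.8.1), and no secondary outcome has a margin. Hematoma, postoperative anemia, lowest Hb and Ht, Hb decrease, bleeding index and red-cell units carry no infection in their definitions. Wound infection and hematoma are separate variables, so many reoperated patients could be classified by cross-tabulation. The article does not say that only a pooled yes or no is stored, and the full data dictionary is not shown. All of this stands and limits the weight of the point. It does not remove it: the article states the definition and its classification, and they do not match.

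A reader might go further and infer that the plan's own hypotheses make the two causes cancel, so that a bleeding harm would be hidden. The documents do not support that. Section 3 hopes early surgery may "lower the risk of complications related to immobilization such as pressure ulcers and nosocomial infections"; this concerns immobilization and says nothing about infection that leads to reoperation. Full cancellation appears only if an equal and opposite infection effect is assumed, and infection could equally move with bleeding.

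Nor does any analysis rule turn a null result on these items into a finding of bleeding safety, although Section 3 does speak broadly of non-inferiority for bleeding and thrombotic complications. Finally, one patient appearing under both reoperation and wound infection is normal for separately reported outcomes and is not an error.

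**Conclusion.** The point holds in a limited form. Sections 4.2 and 5.5.2 place infection-only reoperations and neuropraxias among the bleeding outcomes, so these two items do not isolate bleeding. With similar infection rates in the two groups the bleeding ratio is diluted, for example from 2.0 to 1.33. With differing rates it can shift in either direction. Every size given rests on assumed rates and on no overlap of causes within a patient.

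The primary conclusion and the sample size are unaffected, the events are probably rare, and other bleeding measures stay clean. The weight is optional to minor, and the change is worth making because it is cheap.

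**What to change.** In Sections 4.2 and 5.5.2, record the cause of each reoperation and each sciatic neuropraxia as bleeding, infection or both. Report events caused by bleeding, including those marked both, under bleeding-related outcomes. Report infection-only events under postoperative complications, next to surgical wound infection. The combined item may be reported in addition.

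The category for both causes is needed because a hematoma can become infected. The cost is revised wording and one cause field in REDCap. The cause must already be read from the record to apply the present definition, and the repeated extractions described in Section 5.6 make it practical to add the field during inclusion. The downside is fewer events in each outcome.

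### Stroke is listed as a thrombotic outcome with no ischaemic restriction, and no bleeding outcome names haemorrhagic stroke or intracranial bleeding

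*Protocol article*

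**What the plan says.** Section 5.5.2 assigns each event to a category and names its confirming test: "Thrombotic complications recorded in this study comprise myocardial infarction (confirmed by electrocardiogram), stroke (confirmed by CT"). Pulmonary embolism, deep vein thrombosis and peripheral arterial thrombosis complete that sentence. Section 4.2 uses the same grouping: "To investigate the effect on thromboembolic outcomes in this population (such as acute myocardial infarction, stroke, pulmonary embolism", again without a stroke subtype.

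On the bleeding side, Section 5.5.2 covers transfusion, haemoglobin and haematocrit measures and the bleeding index, and then adds: "Clinical complications such as reoperation due to postoperative bleeding or infection, sciatic neuropraxia due to postoperative bleeding or infection, postoperative hematoma, and postoperative anemia". Section 4.2 gives a similar list of bleeding outcomes, introduced by i.e., so it reads as complete. Neither list names haemorrhagic stroke or any other intracranial bleed.

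Section 5.8.2 sets the analysis: "Binary outcomes, including thromboembolic events, postoperative complications, and a Hb decrease of more than 2 mmol/L, will be analyzed using Chi-square tests". Where expected counts are small, Fisher's exact test takes their place. Section 3 describes the intended conclusion: "If early surgery is shown to be non-inferior with respect to bleeding and thrombotic complications", practice should move toward early surgery.

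**The concern.** The timing question weighs two risks that can move in opposite directions. Operating sooner may raise bleeding, and waiting longer off the anticoagulant may raise thrombosis. A secondary outcome meant to measure one of these should not absorb events that belong to the other.

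The other three events in the thrombotic sentence have names that already specify an embolus or a thrombus. Stroke does not. Its only stated criterion is CT confirmation, which a haemorrhagic stroke also meets. Such an event therefore fits the thrombotic definition as worded and has no named place among the bleeding outcomes. It would not necessarily show up in the primary endpoint either, because an intracranial bleed need not lead to a red-cell transfusion. An intracranial bleed that nobody would call a stroke, such as a subdural haematoma, may have no named place at all.

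What is at stake is the reading of the secondary safety results, on which the Section 3 conclusion about bleeding and thrombosis would partly rest.

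**Working it through.** **1. The plan's own figure, to see what is not affected.** Section 5.7 assumes "an expected event rate of 15% in the control group and 10% in the intervention group" and a 5-point margin. Its error rates are given as a "one-sided alpha of 0.05 (Zα = 1.645) and a power of 90% (Zβ = 1.282"). With unpooled variance:

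n per group = [0.15 × 0.85 + 0.10 × 0.90] × (1.645 + 1.282)² / (0.05 + 0.05)² = 0.2175 × 8.567 / 0.01 = 186.3, rounded up to 187, or 374 in total.

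This reproduces the stated size. No stroke definition enters it.

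**2. The wording side by side.**
- Section 4.2, thromboembolic outcomes: stroke, no subtype.
- Section 5.5.2, thrombotic complications: stroke, no subtype, confirmed by CT.
- Section 4.2, bleeding outcomes (complete list): no intracranial bleed.
- Section 5.5.2, clinical bleeding complications (introduced by such as, so open): no intracranial bleed named.
- No other section restricts stroke to the ischaemic type or says where a haemorrhagic one goes.

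**3. How many events could be affected.** The documents give no rate for stroke or intracranial bleeding, so every rate in steps 3 and 4 is an assumption. If 1% to 2% of 374 patients have a stroke, that is 374 × 0.01 = 3.7 to 374 × 0.02 = 7.5 strokes. If 15% to 25% of these are haemorrhagic, the count is 3.7 × 0.15 = 0.6 to 7.5 × 0.25 = 1.9 events across both cohorts. Zero is also possible.

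**4. Direction.** Suppose, for illustration, that the true thrombotic risk is 2% with early and 3% with delayed surgery, a difference of −1.0 point. Suppose also that every haemorrhagic stroke is counted as thrombotic.

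| Assumed haemorrhagic stroke, early / delayed | Recorded thrombotic risk, early / delayed | Recorded difference |
|---|---|---|
| 1.0% / 0.5% | 3.0% / 3.5% | −0.5 point |
| 0.5% / 0.5% | 2.5% / 3.5% | −1.0 point |
| 0.5% / 1.0% | 2.5% / 4.0% | −1.5 points |

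The same misfiling can shrink, leave or enlarge the difference. The documents do not say which case applies.

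**The case against.** The strongest reply is that the heading qualifies the list. Under thrombotic complications, an ordinary reader takes stroke to mean thromboembolic stroke, and nothing instructs the data extractor to enter a haemorrhage there. That is fair, and it means the misfiling is possible, not certain. It does not settle the matter, because the only stated criterion is a CT finding and no alternative place is named for the haemorrhagic event.

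Several further points reduce the weight of the concern:
- The clinical bleeding list in Section 5.5.2 is open, so a bleed could be added there. The list in Section 4.2 is not open.
- Section 5.3 requires an isolated hip fracture, so an intracranial injury present on arrival would plausibly make the patient ineligible. What remains is mainly new bleeding during admission.
- Section 5.5.2 defines no thrombotic composite, and Section 5.8.2 can be read as testing each event separately. If so, only the stroke row is affected.
- An article condenses a fuller protocol, and subtype coding may sit in the standardized variable set that Section 5.6 mentions. Still, this article itself assigns the category and the test, and that is the text to correct.

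A reader might go further and infer that requiring an ECG for infarction and a CT for stroke means that many infarctions and early ischaemic strokes are missed. The documents do not support this. They give no sensitivity for either test, no share of infarctions without ECG changes and no event rates. An event without a diagnostic finding would not meet the wording, but how often that happens is unknown. Nor is replacing the ECG criterion with a troponin-based one a clear improvement. Cohorts are formed by hospital, so if troponin testing varies by hospital, ascertainment could differ between the cohorts. An objective confirming test is a defensible choice.

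**Conclusion.** The point holds as a definitional gap in a secondary outcome. As worded, a haemorrhagic stroke on a DOAC can be counted as thrombotic and not as bleeding, while Section 3 looks to a conclusion on both. This rests only on the text of Sections 3, 4.2 and 5.5.2 and on the fact that CT confirms either subtype.

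The size cannot be derived from the documents. It is probably small: about 0.6 to 1.9 events among 374 patients under the assumed rates in the working. A reader might also infer that the thrombotic comparison is pushed toward no difference. The documents do not establish that, since the effect depends on which cohort has the haemorrhagic events. The primary transfusion endpoint, the 5% margin and the sample size of 374 are unaffected.

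**What to change.** In Sections 4.2 and 5.5.2:
1. Define the thrombotic outcome as ischaemic stroke, with haemorrhage excluded on imaging already done in routine care.
2. Add haemorrhagic stroke and other intracranial bleeding as a separate bleeding-related outcome. The test rule for binary outcomes in Section 5.8.2 already covers it.
3. Add one stroke-subtype field to the extraction form.

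Optionally, keep ECG-confirmed infarction as defined and also report, as a separate supplementary count, infarctions documented by the treating physician without a diagnostic ECG, noting that this count depends on local testing practice.

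The cost is a few reworded lines and one extra field. No new tests and no change in care are needed. Because Section 5.6 has data extracted retrospectively from the health records at several time points, the subtype can also be sought for patients already included.

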### 5.9. Missing Data

Because of the prospective registration of predefined variables and regular quality checks, we expect minimal missing data. If missing data occur, we will assess their extent and mechanism (missing completely at random, missing at random, or missing not at random). When appropriate, we will apply multiple imputation using chained equations to minimize bias and preserve statistical power.

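### Time to DOAC restart and total time without DOAC are undefined for patients who never restart, so the planned tests compare restarters only

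*Protocol article*

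**What the plan says.** Section 5.5.2 of the Protocol article defines two intervals that end at the same event: "time until DOAC therapy is restarted after surgery (in hours, defined as the time between end of surgery and first postoperative DOAC dose" and "total time without DOAC therapy (in hours, defined as the time between last DOAC intake and the first postoperative DOAC dose". Neither definition says what happens when that dose is never given. In the same sentence, hospital length of stay is "defined as the time between ED presentation and discharge from hospital or in-hospital death", so death closes that interval explicitly.

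Section 5.8.2 fixes the type of variable: "Continuous variables (i.e., Hb decrease, bleeding index, surgery duration, time to DOAC restart, hospital length of stay". It then fixes the tests: "Normally distributed outcomes will be analyzed using parametric tests, specifically independent-sample t-tests", and "If the distribution is non-normal, non-parametric methods, such as the Mann–Whitney U test, will be applied". It names time to restart but not total time without DOAC, which as a duration in hours falls under the same rule.

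Section 5.9 offers one general provision for absent values: "When appropriate, we will apply multiple imputation using chained equations to minimize bias and preserve statistical power". Section 5.6 gives the participating hospitals' electronic records as the data source and describes no collection of doses after discharge. In-hospital death is itself a recorded outcome in section 5.5.2: "in-hospital mortality (recorded in hospital records), and 30-day mortality (determined through municipality records".

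**The concern.** Both tests need one completed number per patient, and a patient without a postoperative dose has none. This is not ordinary missingness: the value does not exist, and the reason for its absence (death, or a DOAC still withheld after bleeding) lies close to the outcomes being compared. Multiple imputation would give such a patient a restart time resembling those of patients who did restart.

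Two things are at stake. First, the reported interruption is too short as a description of the whole cohort. Second, if the cohorts differ mainly in how many patients fail to restart, the planned test cannot see it. Readers are likely to set time off anticoagulation beside the thromboembolic results when judging early against delayed surgery, although the article plans no formal analysis linking them.

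**Working it through.** **The plan's own figure.** The article states no number for these outcomes. Its only sample-size figure, in section 5.7, reproduces: (0.15 × 0.85 + 0.10 × 0.90) × (1.645 + 1.282)² / (0.05 + 0.05)² = 0.2175 × 8.567 / 0.01 = 186.3, hence 187 per group. It concerns the primary outcome; only the group size is used below.

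**Which patients have a value**

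| Patient | Time to restart | Total time without DOAC |
|---|---|---|
| Restarts in hospital | defined | defined |
| Dies before restart | undefined | undefined |
| Discharged without restart | undefined if only hospital doses are captured | same |

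**What a restarter-only median estimates.** If a fraction m has no value and all of them would have had longer times than the restarters, the reported median is the (1 − m)/2 quantile of the whole cohort. For m = 5%, 10% and 20% that is the 47.5th, 45th and 40th percentile. This does not apply to early deaths.

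**Within-cohort size, first set of assumptions.** Restart times are lognormal with log-SD 0.8. Discharge is lognormal with median 144 h and log-SD 0.5. In addition, 0% or 10% never restart. There are 400,000 simulated patients per row and no deaths. The all-patient median counts restarts after discharge at their unseen time and ranks patients who never restart as longest.

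| Restart median | Never restart | No value | Restarters' median | All-patient median | Shortfall |
|---|---|---|---|---|---|
| 24 h | 0% | 2.8% | 23.3 h | 24.0 h | 0.7/24.0 = 3% |
| 24 h | 10% | 12.6% | 23.3 h | 26.8 h | 3.5/26.8 = 13% |
| 48 h | 0% | 12.3% | 42.5 h | 48.1 h | 5.6/48.1 = 12% |
| 48 h | 10% | 21.0% | 42.5 h | 53.7 h | 11.2/53.7 = 21% |
| 72 h | 0% | 23.1% | 57.1 h | 71.9 h | 14.8/71.9 = 21% |
| 72 h | 10% | 30.9% | 57.3 h | 80.7 h | 23.4/80.7 = 29% |

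**Second, milder set.** Usual restart has median 36 h (log-SD 0.5), a withheld subgroup has median 168 h, and discharge has median 144 h (log-SD 0.3 to 0.5). With 5% withheld the median moves from about 37 to 36 h (roughly 2% to 4%). With 20% withheld it moves from about 42 to 38 h (roughly 10%). The mean moves more: from 48 to 42 h (6/48, about 13%) and from 71 to 48 h (23/71, about 32%).

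**What the planned test can see.** Suppose 5% against 15% never restart, restarters are otherwise alike, and there are 187 per group (4,000 runs). Mann–Whitney on restarters rejects in 5% of runs, which is its nominal error rate. Counting patients who never restart as longest raises this to 39%. Comparing the two proportions directly gives an expected z of 0.10 / √[(0.05 × 0.95 + 0.15 × 0.85)/187] = 0.10 / 0.0306 = 3.27. The signal therefore lies in the proportion that the planned test discards.

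**When restart itself is slower.** With true restart medians of 48 and 60 h and 5% never restarting in both groups, the restarter-only difference in medians averages 7.9 h, against 12.6 h over all patients (2,000 runs).

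**The case against.** The best reply is that an article may leave the scoring of patients without an event to an analysis plan. Nowhere does it prescribe complete-case analysis, its wording on non-parametric methods is open-ended, and imputation is conditional on being appropriate. Part of this stands: dropping patients is the consequence of the definition and the tests, not a stated rule. But the article does fix the endpoint, its type and its tests, and that combination has no place for a patient who does not restart. Length of stay shows that the authors closed an interval for death where they thought of it.

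Other objections stand and limit the point.

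- Loss at discharge is inferred from the data source. Only death before restart certainly leaves the interval undefined.
- A reader might infer that the patients lost are always those with the longest interruptions. That suits patients discharged without restart. An early death can end a short interruption and is a competing event.
- A reader might infer that the cohorts are made to look more alike, or that one is favoured. That requires different rates of non-restart, and the article gives none.
- A reader might take the fall in the mean as the size. Data this skewed would go to the Mann–Whitney test, and the effect on the median is smaller.
- Two obvious repairs are themselves questionable. Censoring at discharge assumes that those patients later restart like the ones still in hospital, and ranking every non-restarter as longest gives a day-1 death the longest interruption.
- Neither interval appears in the secondary objectives (section 4.2), and thrombotic events, bleeding and mortality are each analysed directly.

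**Conclusion.** The point holds as a minor one. As defined, both intervals have no value for patients who die before restart and, if capture ends at discharge, for those who leave without restart. The planned tests then describe and compare restarters only. Interruption over the whole cohort is understated, and a difference confined to the proportion not restarted goes undetected.

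Under the assumed inputs the within-cohort median is too short by about 3% to 29% in the first set and about 2% to 10% in the milder one. These ranges rest on assumed restart and discharge distributions and assumed shares of non-restart, and they include no deaths. The actual size, and the direction of any bias between early and delayed surgery, cannot be computed from the article. Only additional secondary outcomes are touched; the non-inferiority analysis and the 187 per group are not.

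**What to change.** In sections 5.5.2 and 5.8.2:

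- Analyse both intervals as time to the first DOAC dose after surgery, using cumulative incidence functions, with death before restart and discharge without restart as competing events. Do not censor at discharge, since that censoring is likely to be informative.
- Report per cohort the proportion not restarted by discharge and the proportion who died before restart.
- Label any median or test among restarters as conditional on restart.
- Name total time without DOAC alongside time to restart in section 5.8.2, and state whether doses after discharge are captured.

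In section 5.9, exclude patients known to have died or been discharged without restart from imputation of these two intervals.

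The cost is analysis wording and a little extra analysis work. The times needed already underlie outcomes that the article defines. With no censoring, the cumulative incidence at a given time is the number restarted by then divided by all patients in the cohort. Nothing about patient care changes.
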